#### Secondary Outcomes

Secondary outcomes for the ICU work packages include ICU mortality; in-hospital mortality; hospital length of stay (the number of days from the date of ICU admission to date of ICU discharge or death); mechanical ventilation duration (total duration of mechanical ventilation in days); and ventilator-free days, and alive at day 28. In all 4 work packages, we will evaluate the incidence of general systemic complications during the hospital stay as a secondary outcome, including myocardial infarction, deep venous thrombosis, pulmonary embolus, hyperglycemia, acute kidney injury, and sepsis. The definition of the various general systemic complications is shown in Table S1 in Multimedia Appendix 1.

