### Study Aims

#### Work Package 1: High-Dose Corticosteroid Treatment in the Ward

Work package 1A (WP1A) is used to investigate whether initial treatment with high-dose corticosteroids compared to treatment with 6 mg dexamethasone per day for 10 days, or an equivalent corticosteroid, improves patient outcomes in the ward (Figure 1).

WP1B is used to investigate whether treatment with high-dose corticosteroids compared to no corticosteroids, after treatment with 6 mg dexamethasone per day for 10 days, improves patient outcomes in the ward.

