#### Work Package 3: High-Dose Corticosteroid Treatment After Standard Corticosteroid Treatment in the ICU

Work package 3 (WP3) is used to investigate whether treatment with high-dose corticosteroids compared to no corticosteroids, after treatment with 6 mg dexamethasone per day for 10 days, improves patient outcomes in the ICU.

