### Patient Selection and Inclusion Criteria

Adult patients (≥18 years) hospitalized with polymerase chain reaction–confirmed COVID-19 or high clinical suspicion of COVID-19 will be included (Figure 3). Pregnant patients and patients receiving corticosteroids for other conditions during or prior to hospital admission are eligible, although a prespecified sensitivity analysis excluding these patients will be performed. Patients who die within 48 hours after admission or patients who object to participate will be excluded from the study. In WP1 and WP4, we will include patients from all SARS-CoV-2 epidemic waves, and in WP2-3, we will include patients from the first and second waves only. Specific inclusion and exclusion criteria for each work package will be applied. In WP1A, patients will be included who are admitted to the ward with a World Health Organization clinical progression scale class of 4-5 [19] (ie, no oxygen or oxygen therapy via a cannula or [non-rebreather] mask). WP1B includes patients who have progressed to the World Health Organization clinical progression scale class of 5-6 (ie, noninvasive oxygen therapy, including conventional oxygen via cannula [non-rebreather] mask, high-flow nasal cannula, noninvasive continuous positive airway pressure, and noninvasive bilevel positive airway pressure) after in-hospital treatment with 10 days of 6 mg per day dexamethasone. The study population for WP2-4 consists of patients admitted to the ICU for a period exceeding 48 hours, who received invasive mechanical ventilation via an endotracheal tube, a tracheostomy, or extracorporeal membrane oxygenation during their ICU stay.

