### Interventions

Patients were administered with >6 mg dexamethasone or an equivalent corticosteroid for a minimum of 3 consecutive days (Table 1). Our study permits the use of other general concurrent interventions, such as venous thromboembolism prophylaxis, fever and glucose control, fluid management, antibiotics, and antiviral drugs. The use of other immunomodulatory agents such as baricitinib, JAK inhibitors, and interleukin 6 pathway inhibitors, as well as antiviral drugs such as remdesivir, is allowed as part of a clinical trial or hospital policy. However, a sensitivity analysis will be performed excluding these patients.

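### The outcome labelled hospital length of stay is an ICU interval that death also closes, and the complication window in WP1B, and probably WP3, opens before the treatment contrast begins

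*Protocol article*

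**What the plan says.** All of this is in the protocol article.

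- **Length of stay.** Under Secondary Outcomes, the ICU work packages list "hospital length of stay (the number of days from the date of ICU admission to date of ICU discharge or death". Beside it stand ICU mortality, in-hospital mortality, "mechanical ventilation duration (total duration of mechanical ventilation in days", and ventilator-free days.
- **Complications.** The same section says that for all four work packages "we will evaluate the incidence of general systemic complications during the hospital stay as a secondary outcome". On definitions it adds: "The definition of the various general systemic complications is shown in Table S1 in Multimedia Appendix 1". That appendix is not shown.
- **Start of the contrast.** Under Study Aims, WP3 poses this question: "treatment with high-dose corticosteroids compared to no corticosteroids, after treatment with 6 mg dexamethasone per day for 10 days, improves patient outcomes in the ICU". WP1B puts the same question for the ward. Under Patient Selection and Inclusion Criteria, WP1B patients enter once they have progressed "after in-hospital treatment with 10 days of 6 mg per day dexamethasone".
- **Analysis.** Statistical Analysis makes exposure a yes/no variable in the primary analysis. It mentions time-dependent exposure only as a possible Cox model for death, and competing-risk methods only as something that may be explored. Neither is tied to length of stay or complications.

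**The concern.** There are two separate problems of timing.

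First, the label and the definition of the length-of-stay outcome disagree. Ward days before and after intensive care are left out, so hospital stay is not captured. Staff at 22 hospitals could follow either the label or the definition. Because the clock stops at death as well as at discharge, a shorter mean can reflect faster recovery or more deaths.

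Second, the complication window is the hospital stay, while the WP1B and WP3 contrasts start late in that stay. A thrombosis or sepsis episode during the preceding low-dose course cannot have been caused by the later choice between high-dose treatment and none, yet it falls inside the window. Safety matters here: the Introduction names secondary infection as a possible cost of high-dose treatment, and sepsis is a listed complication.

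**Working it through.** The article gives no rate, duration or sample size for these outcomes, so there is no figure of its own to reproduce. The label mismatch needs no arithmetic. Every input below is an assumption chosen to show direction and range.

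**1. Stay closed by death**

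Mean stay = m × L_dead + (1 − m) × L_surv, where m is mortality, L_dead the mean day of death and L_surv the survivors' mean stay. Hold L_dead and L_surv equal in both groups and raise m from 30% to 40%. The mean then shortens by 0.10 × (L_surv − L_dead).

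Example with L_surv = 20 and L_dead = 10: 0.30 × 10 + 0.70 × 20 = 17.0 days; 0.40 × 10 + 0.60 × 20 = 16.0 days; shift 1.0 day.

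| Survivors' stay (days) | Death at day 8 | Day 10 | Day 14 |
|---|---|---|---|
| 16 | 0.8 | 0.6 | 0.2 |
| 20 | 1.2 | 1.0 | 0.6 |
| 25 | 1.7 | 1.5 | 1.1 |

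The range is 0.2 to 1.7 days. Lowering mortality to 20% lengthens the mean by the same amounts.

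**2. Complications counted over the whole stay**

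Risk of any complication = 1 − (1 − pre) × (1 − post), taking risks before and after exposure as independent. Assume a true post-exposure risk of 20% treated and 15% control: difference +5.0 points, ratio 1.33.

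With equal pre-exposure risk p, the difference is (1 − p) × 5.0 points:

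| p | Treated | Control | Difference (points) | Ratio |
|---|---|---|---|---|
| 10% | 28.0% | 23.5% | +4.5 | 1.19 |
| 20% | 36.0% | 32.0% | +4.0 | 1.13 |
| 30% | 44.0% | 40.5% | +3.5 | 1.09 |
| 40% | 52.0% | 49.0% | +3.0 | 1.06 |

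Balanced early events dilute the effect and never change its sign.

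With unequal pre-exposure risk:

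- 10% treated, 20% control: 1 − 0.90 × 0.80 = 28.0%; 1 − 0.80 × 0.85 = 32.0%. The difference is −4.0 points, so the sign reverses.
- With 10% in the treated group, reversal starts once the control risk exceeds 1 − 0.72/0.85 = 15.3%.
- 20% treated, 10% control: 36.0% against 23.5%. The difference is +12.5 points, so the harm is exaggerated.

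Counting from the index day returns the assumed 20% against 15%.

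**3. Which work packages are affected**

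In WP1B the 10 days are stated to be in hospital, so at least 10 days of the window precede the contrast. In WP3 the course also comes first, but the text does not say where it was given; an in-hospital course is an inference. WP1A and WP2 concern initial treatment, so fewer days are at issue.

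**The case against.** The best defence has four parts.

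- **Convention.** Ending a stay at discharge or death is common practice, and the definition is usable once read as ICU stay. Mortality is listed beside it and 28-day survival is a primary outcome for WP2 and WP3, so a rise in deaths would be visible. This stands, and it limits the danger of misreading. It does not repair the label, and it does not say how deaths enter the comparison of durations.
- **Ventilation duration.** A reader might infer that this outcome has the same stated fault. The text gives only a total in days, with no rule about death, and ventilator-free days are listed as a companion. The documents do not support charging it with the same error.
- **Complications.** The article never says that early events will be attributed to treatment; incidence could mean new events after cohort entry, and the appendix could hold onset rules. This lowers certainty. Still, the main text sets the window as the hospital stay. Prior complications are not among the named covariates, although the list may be changed.
- **Reversal.** A reader might infer that the window by itself makes harm look like benefit. It does not. Both groups share the preceding regimen, and balanced early events only dilute. Imbalance is plausible, because the Discussion concedes bias by indication, but the documents give no evidence of its size.

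**Conclusion.** The label error is certain and rests on no assumption: as written, an ICU interval would be reported as hospital stay.

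The effect of deaths on that interval is real in direction and modest in size: 0.2 to 1.7 days for a 10-point change in mortality, given survivors' stays of 16 to 25 days and deaths at days 8 to 14. The single figure of 1.0 day is one scenario within that range and should not be quoted alone.

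The complication window is badly placed for WP1B, and for WP3 if the preceding course was given in hospital. The expected consequence is dilution, from +5.0 to between +4.5 and +3.0 points under the assumed risks. Pre-exposure events reverse the sign only if they are unequal between groups.

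These are secondary outcomes. The point should be corrected, but it does not touch the primary comparison.

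**What to change.** 1. Rename the current item ICU length of stay, or define hospital length of stay with its end at hospital discharge and its start stated. If both are wanted, list both.
2. State how deaths are handled. Either analyse time to discharge alive with death as a competing event, or report stay in survivors alongside mortality. The second option conditions on survival, so it should be read as descriptive.
3. For WP1B and WP3, count only complications with onset after the work package's index day. Define that day by the same rule in both groups, since the comparator has no start of treatment. Enter earlier complications as a baseline covariate.

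Items 1 and 2 are wording and use admission, discharge and death dates that are routinely recorded. Item 3 has a real but small cost: complication onset dates must be extracted, from databases that already exist. The article expected data collection to run until December 2023.

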### Statistical Analysis

Data will be analyzed on a convenience sample. No sample size calculations are considered for the study nor will they be provided post hoc [23]. The use of high-dose corticosteroids will be defined as a dichotomous variable (yes or no) in primary analysis and as a continuous variable in secondary analysis.

To study between-center variation in corticosteroid dosing strategy, the proportion of individuals who received high-dose corticosteroids will be compared across hospitals. Determinants of receiving high-dose corticosteroids will be evaluated using a multivariable logistic regression model with study center forced in the model. Whether the effects of significant determinants are different across centers will be tested through a determinant × center interaction term added for each determinant, separately.

In WP1, WP2, and WP3, several statistical analysis approaches will be considered to determine the association between high-dose corticosteroids and outcome, and statistical analyses will depend on the structure of the available data. A multivariable logistic regression model will be used with high-dose corticosteroids as exposure and survival at day 28 as an outcome. Covariates used for adjustment will include age, gender, BMI, smoking status, prior administration of corticosteroids during admission, comorbidity, sequential organ failure assessment score, oxygen saturation, partial pressure of oxygen in arterial blood–fraction of inspiratory oxygen concentration ratio, C-reactive protein, procalcitonin, ferritin, interleukin 6, D-dimer, lactate dehydrogenase, platelet count, lymphopenia, and level of respiratory support. Covariates can be added or removed based on insights from the data set or from the literature. A model might be constructed in which patients are matched on a propensity score based on their probability to receive high-dose corticosteroid treatment. Propensity scores will be determined using a logistic regression model with high-dose corticosteroids as a dependent variable and determinants of high-dose corticosteroids as independent variables. After matching, survival and mortality at day 28 and other outcome parameters will be compared between matched groups using logistic regression. A Cox proportional hazards model might be performed to determine the effect of high-dose corticosteroids on time to death while taking into account the days of administration using time-dependent covariates. Other approaches involving censoring weights for differential loss to follow-up (eg, marginal structural models) or competing risks (eg, joint models) might be explored.

Furthermore, we will use clinical and biological data to perform latent class analysis to search for subphenotypes, which respond more favorably to corticosteroid treatment. This heterogeneity of treatment effect will be evaluated by including the latent class analysis-derived subphenotype, corticosteroid exposure, and an interaction term of the 2 as c-variate in the above-described survival models. Heterogeneity of treatment effect is considered to be present if the interaction term has a *P* value of <.05.

Regarding WP4, patients are randomly selected and cases will be patients treated with high-dose corticosteroids, whereas controls will be patients who were not treated with high-dose corticosteroids. In WP4a, inverse probability treatment weighting and inverse probability of censoring weights will be used together in a marginal structural model. After we have analyzed the effect of high-dose corticosteroids on mortality and the other outcome measures, we will use this model to determine if the listed biomarkers modify the effect of high-dose corticosteroids on mortality.

In WP4b, we will identify transcriptome features that are differentially altered between cases and controls. Mean transcriptome levels will be compared using an unpaired *t*-test and *P* values will be adjusted for false-discovery rate using the Benjamini-Hochberg procedure. The log_2_ mean fold change of levels between cases and controls will also be calculated for each transcriptome. We will define transcriptome features as those with an adjusted *P* value of <.05 and a >2.0 or <–2.0 log_2_ mean fold change in level.

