## Methods

### Definition High-Dose Corticosteroids

High-dose corticosteroids are defined as every treatment with dexamethasone >6 mg daily or an equivalent corticosteroid (Table 1). Regarding prior and continuing use of corticosteroids for other conditions, corticosteroids are considered as part of the COVID-19–related intervention when the high-dose threshold is passed.

**Table 1 table1:** Equivalent corticosteroids and dosages (total daily dosing)^a^.

Drug	Equivalent dose (mg)	Low-dose (mg)	High-dose (mg)
Dexamethasone	0.75	≤6	>6
Cortisone	25	≤200	>200
Hydrocortisone	20	≤160	>160
Prednis(ol)one	5	≤40	>40
Methylprednisolone	4	≤32	>32
Bethamethasone	0.75	≤6	>6

^a^This table shows the equivalent corticosteroids and dosages. The equivalent dose is derived from Farmacotherapeutisch Kompas [18].

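### One high-dose yes/no exposure is fixed for work packages whose aims need different comparators, and the two definitions of high-dose disagree on duration

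*Protocol article*

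**What the plan says.** **Exposure.** Under Statistical Analysis: "The use of high-dose corticosteroids will be defined as a dichotomous variable (yes or no) in primary analysis". A continuous version is kept for secondary analysis. The same section plans, for WP1, WP2 and WP3, a multivariable logistic model with high-dose use as exposure and day-28 survival as outcome. For WP4 it adds that "controls will be patients who were not treated with high-dose corticosteroids".

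**Aims.** WP1A and WP2 ask about "initial treatment with high-dose corticosteroids compared to treatment with 6 mg dexamethasone per day for 10 days" (or an equivalent drug), on the ward and in the ICU respectively. WP1B asks about "treatment with high-dose corticosteroids compared to no corticosteroids, after treatment with 6 mg dexamethasone per day for 10 days", and WP3 asks the same in the ICU.

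**Definition.** Under Definition High-Dose Corticosteroids: "High-dose corticosteroids are defined as every treatment with dexamethasone >6 mg daily or an equivalent corticosteroid". Under Interventions: "Patients were administered with >6 mg dexamethasone or an equivalent corticosteroid for a minimum of 3 consecutive days".

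**The concern.** For a yes/no variable to estimate the stated contrast, *no* has to mean low-dose in WP1A and WP2, and no corticosteroid in WP1B and WP3. *Yes* has to mean high-dose from the start in the first pair, and high-dose after a completed low-dose course in the second. The variable as described carries neither distinction.

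The study sets out to inform dosing and timing. If *no* mixes untreated with low-dose patients, the dosing contrast is blurred. If patients who deteriorate on low-dose and are then escalated count as *yes*, poor outcomes of the low-dose strategy are charged to high-dose, and the timing question is distorted too.

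**Working it through.** **1. Aims set against listed eligibility** (Study Aims; Patient Selection and Inclusion Criteria)

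| | *Yes* should mean | *No* should mean | What listed eligibility leaves open |
|---|---|---|---|
| WP1A | high-dose from the start | low-dose course | WHO class 4-5, including patients without oxygen; no corticosteroid required |
| WP2 | high-dose from the start | low-dose course | ICU stay over 48 h with invasive ventilation; no corticosteroid required |
| WP1B | high-dose after the low-dose course | none after it | prior course required, but not that corticosteroids then stop |
| WP3 | high-dose after the low-dose course | none after it | same population sentence as WP2; no prior course listed |

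- *Untreated patients.* The Introduction ties the low-dose recommendation to oxygen need, so WP1A patients without oxygen may be untreated and would be coded *no*. The Figure 3 legend words class 4 like class 5, but the inclusion text names the no-oxygen category outright.
- *Escalators.* The Introduction acknowledges that some patients who do not respond to dexamethasone are escalated, and that high-dose is given mainly late and in the most severe disease. If every treatment above the threshold counts and no start window is set, they become *yes* in WP1A and WP2.
- *Continuers.* In WP1B and WP3, patients who stay on low-dose are *no*, although the stated comparator is none.
- *WP2 and WP3.* They have the same listed population, exposure variable, primary outcomes and model, so the text does not separate their two contrasts.

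**2. The two definitions.** The cut-offs in Table 1 reproduce as equivalent dose × 6/0.75, that is × 8: 0.75 → 6, 25 → 200, 20 → 160, 5 → 40, 4 → 32 mg. The definitions therefore agree on dose and differ only on duration. One or two days above the threshold is high-dose under the first and not under the second. The second also makes exposure depend on surviving long enough to complete it.

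**3. Illustration.** The plan has no figure to reproduce. All risks and proportions below are assumptions. The odds ratios (OR) are crude, for mortality, high-dose *yes* against *no*.

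(a) *Untreated in no.* The true risk is 20% on initial high-dose and on low-dose (OR 1.00). Let u be the untreated share of *no* and r their risk: p0 = (1 − u) × 0.20 + u × r.
- r = 0.10, u = 0.1 to 0.5: p0 = 0.19 to 0.15, OR 1.07 to 1.42.
- r = 0.30, u = 0.1 to 0.5: p0 = 0.21 to 0.25, OR 0.94 to 0.75.

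(b) *Escalators in yes.* 500 start high-dose and 1000 start low-dose, with 20% mortality in both (OR 1.00). A fraction f of low-dose starters escalates, with mortality m: p_yes = (100 + 1000fm)/(500 + 1000f); p_no = (200 − 1000fm)/(1000(1 − f)).
- f = 0.05, m = 0.30: 115/550 = 0.209 against 185/950 = 0.195, OR 1.09.
- f = 0.20, m = 0.50: 200/700 = 0.286 against 100/800 = 0.125, OR 2.80.

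A second set of assumptions (10-20% escalated, mortality 40-45% against 15-18% in the rest, 30-50% of all starting high-dose) gives OR 1.28 to 2.27. At the upper end, low-dose starters have risk 0.2 × 0.45 + 0.8 × 0.15 = 0.21. Then p_yes = (0.3 × 0.21 + 0.7 × 0.2 × 0.45)/(0.3 + 0.14) = 0.286 against p_no = 0.15.

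(c) *Low-dose continuers in no (WP1B, WP3).* Assumed truth: high-dose 24%, none 30%, so OR = (0.24/0.76)/(0.30/0.70) = 0.74. With continuers at 10-50% of *no*:
- their risk 24%: OR 0.76 to 0.85.
- their risk 36%: OR 0.72 to 0.64.

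**The case against.** A dichotomous variable is a proper coding of a two-arm contrast once the population is restricted, and the sentence on the exposure may only mean dichotomous as opposed to continuous. The aims themselves say initial, which sits badly with coding a later escalator as *yes*. Work-package-specific criteria are announced, Figure 3 on inclusion is not shown, and WP1 seeks low-dose centers for comparison. Time zero and the handling of switchers are often left to a statistical analysis plan. The model adjusts for prior corticosteroids during the admission, oxygen saturation and level of respiratory support, and a Cox model with time-dependent covariates is listed as an option.

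Much of this limits the point. Misplacement is what the listed text permits, and unseen criteria could narrow it. The odds ratios ignore the covariates, and they concern mortality, whereas for WP1A patients without care restrictions the primary outcome is need for high-flow or invasive ventilation.

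It does not remove the point. The protocol positively fixes the primary exposure and applies one model across WP1 to WP3. The criteria it lists do not set the comparator's corticosteroid status, and the WP4 controls show *no* being used for everyone not on high-dose. Adjusting for prior corticosteroids does not redefine a comparator or a time zero. Choosing low-dose centers does not classify patients. The time-dependent model only might be fitted.

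**Conclusion.** The point holds: the primary exposure as fixed does not carry the contrasts in the aims, and the two definitions of high-dose conflict on duration. Under the assumptions shown, counting escalators as *yes* biases against high-dose. Pooling untreated patients biases in either direction, and against high-dose if they are the lower-risk patients, as those without oxygen plausibly are. Pooling low-dose continuers can also go either way. Size and net sign depend on proportions and risks that the documents do not give.

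Three stronger readings are tempting but unsupported:
- That these patients will certainly be misplaced, so that the estimate answers none of the aims. The work-package criteria not shown could prevent part of it.
- That the conflict of definitions causes this misplacement. It moves only patients with one or two days above the threshold.
- That the errors offset each other, or that the odds ratios above predict the study's bias. In WP1A both errors could run against high-dose, and the figures are unadjusted and assumed.

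**What to change.** For the primary analysis, define exposure, comparator and time zero for each work package to match its aim.

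- **WP1A, WP2:** classify by the regimen started at time zero, keep later escalators in their starting group, and leave patients who start no corticosteroid outside the primary contrast.
- **WP1B, WP3:** restrict to patients who completed the prior course, compare high-dose with none, and keep low-dose continuers as a separate level.
- **Sensitivity analysis:** a time-varying exposure analysis can serve here. It answers a different but legitimate question about escalation.
- **Definition:** reconcile the sections Definition High-Dose Corticosteroids and Interventions into one definition of high-dose used throughout. Which duration rule applies is for the investigators to decide.

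The cost is protocol wording, recoding of the daily type and dose data that the Data Collection section already provides for, and fewer patients in each primary contrast.

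### The analysis of who receives high-dose corticosteroids, and of hospital variation, ignores time at risk, so where treatment can start on different days it mixes prescribing with length of stay

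*Protocol article*

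**What the plan says.** The Statistical Analysis section of the protocol article fixes the following.

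- Exposure coding: "The use of high-dose corticosteroids will be defined as a dichotomous variable (yes or no) in primary analysis and as a continuous variable in secondary". No start of the clock and no window is attached to the yes/no variable.
- Hospital variation: "the proportion of individuals who received high-dose corticosteroids will be compared across hospitals".
- Determinants: "Determinants of receiving high-dose corticosteroids will be evaluated using a multivariable logistic regression model with study center forced in the model".
- Carry-forward to centre interactions: "Whether the effects of significant determinants are different across centers will be tested through a determinant × center interaction term added for each determinant, separately".
- Carry-forward to the propensity score: "Propensity scores will be determined using a logistic regression model with high-dose corticosteroids as a dependent variable and determinants of high-dose corticosteroids as independent variables". The matching itself is optional: "A model might be constructed in which patients are matched on a propensity score based on their probability to receive high-dose corticosteroid treatment".

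Other sections bear on when a patient can become a yes.

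- Interventions describes treatment above the threshold "for a minimum of 3 consecutive days".
- The Introduction says that high dose is given mostly late in the illness and to the sickest patients.
- Study Aims words WP1A and WP2 as comparisons of initial treatment, and WP1B and WP3 as treatment after a 10-day standard course.
- Patient Selection excludes deaths within 48 hours of admission and, for WP2 to WP4, requires more than 48 hours in the ICU.
- Data Collection says that corticosteroid type, dose and route are recorded daily.

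**The concern.** A patient can be recorded as treated only while still in hospital, and under the three-day rule only after staying long enough to complete it. Death and discharge therefore compete with receipt. If starts are spread over the stay, a logistic model of receipt yes/no estimates a mixture of two things: how readily clinicians start high dose, and how long patients remain available to be started. A characteristic that only shortens the stay then looks like a reason not to prescribe. A hospital with shorter stays looks like a low prescriber.

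The Discussion names the identification of factors behind treatment allocation as the initial analysis step against bias by indication. The hospital comparison is the plan's measure of variation in dosing strategy. Both are stated as analyses that will be done. Determinants found significant go on to the centre-interaction tests, and the determinants supply the propensity model if one is built.

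**Working it through.** **Is there a figure to reproduce?** No. The document gives no start rate, length of stay or expected proportion treated. All rates below are assumptions. The three-day minimum is from Interventions. The n of 1500 is the number of patients collected by April 2023 (Results); n=500 is illustrative.

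**Closed form.** Let high dose start at constant daily rate h and patients leave (death or discharge) at constant daily rate d. Then

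P(treated) = h/(h+d), so odds = h/d.

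For a factor that leaves h unchanged and multiplies d by HR, the odds ratio is (h/(d·HR))/(h/d) = 1/HR, whatever h is. HR 1.5 gives 0.67 and HR 2.0 gives 0.50. In terms of mean stay, the odds ratio is the ratio of the two mean stays.

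**Simulation with the three-day rule.** Daily start probability 0.05, daily exit probability 0.08, at least 3 treated days, 28-day horizon, a factor with 50% prevalence and no effect on starting; two-sided 5% test. Ranges cover repeated runs.

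| Exit HR | Odds ratio | Declared significant, n=500 | n=1500 |
|---|---|---|---|
| 1.25 | 0.79 | about 22% | 51–56% |
| 1.5 | about 0.65 | 58–61% | about 97% |

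Analysing the same data as starts per person-day at risk gives about 4–5% throughout.

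**Sensitivity to the assumptions.** In the closed form with n=1500 (750 v 750), mean stays of 8 v 10 days give an odds ratio of 0.80 at every start rate. The chance of declaring it significant is 34% at h=0.02, 51% at h=0.05 and 25% at h=1.0. Mean stays of 7 v 10 days at h=0.05 give 0.70 and 88%.

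**Hospitals.** Same start rate of 0.05/day, mean stays of 8 and 12 days:

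- 0.05/(0.05 + 1/8) = 0.05/0.175 = 28.6%
- 0.05/(0.05 + 1/12) = 0.05/0.1333 = 37.5%

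The crude comparison shows 29% v 38% treated with identical prescribing.

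**When the bias disappears.** With stays of 7 v 10 days and n=1500, but treatment decided at admission, the odds ratio is 1.00 and the rejection rate 5.3%. With starts counted only in a 48-hour window among patients who all stay longer than 48 hours, the odds ratio is 1.00 and the rate 5.0%.

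**The case against.** The case on the other side has several parts, and some of it stands.

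- *The text does not say ever received over the whole stay.* Correct. It says received and yes/no, and a window may be set in a full protocol or analysis plan that is not shown. But the article does fix the method (crude proportions and a logistic model of receipt), and nothing in it ties receipt to a defined moment.
- *WP1A and WP2 concern initial treatment.* This stands. If the decision is made at entry, there is no bias. A reader might rank WP2 among the worst affected because ICU treatment can start late; its stated aim does not support that. In WP1B and WP3, decisions clustered at the end of the 10-day course would also shrink the bias below the constant-rate figures.
- *Death and discharge can pull in opposite directions.* This stands. Assume death at 0.02/day and discharge at 0.06/day, total 0.080. A factor that doubles death and multiplies discharge by 0.7 gives 0.040 + 0.042 = 0.082, and an odds ratio of 0.080/0.082 = 0.98.
- *The plan offers time-dependent Cox and marginal structural models.* For WP1 to WP3 these are optional and concern the association with outcome. They do not replace the determinants model or the hospital comparison.
- *The propensity score is optional, and a factor that predicts early death or discharge is prognostic, so including it is not in itself harmful.* This stands. A reader might infer that the estimated effect of high dose is biased through the score. The material does not show that, and no such bias has been computed.

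**Conclusion.** The concern holds for WP1B, WP3, any pooled analysis and the crude hospital proportions, wherever starts are spread over the stay. There, the planned analysis cannot separate prescribing from length of stay. Under the assumed rates the distortion is material: an odds ratio of about 0.65 for a factor with no effect on prescribing and an exit hazard ratio of 1.5, and a 9-point gap between two hospitals that prescribe alike.

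It would be too strong to say that every factor that shortens the stay will be falsely declared a determinant. At an exit hazard ratio of 1.25 this happens in about 22% of samples at n=500 and 51–56% at n=1500, and it falls to the nominal level if treatment is decided at entry. A factor that affects both stay and prescribing gets a distorted estimate, not a purely false one. The size rests on constant daily rates, a single binary factor and values that the document does not supply. The direction follows from the competing-event structure alone.

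**What to change.** 1. **WP1A and WP2:** define receipt as starting high dose within a fixed early window after entry, among patients still in hospital when that window ends. The logistic model can then stay.
2. **WP1B, WP3 and pooled analyses:** state time zero (for WP1B and WP3, completion of the 10-day course). Replace the yes/no logistic model with a time-to-start model: a cause-specific hazard, or pooled logistic regression by patient-day, with death and discharge as competing events. Use covariates known at time zero or, where available, before the day in question, and keep centre in the model as now planned.
3. **Hospital variation:** compare starts per patient-day at risk, or cumulative incidence of starting by a fixed day, in place of the crude proportion.
4. **Propensity score, if used:** fit it to the same windowed or time-to-start exposure.

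Cost: the daily corticosteroid records already collected must be reshaped to patient-days. Patients who leave before the early window closes are lost from the WP1A and WP2 determinants analysis. A day-specific score requires matching within risk sets, which is more work than a single match per patient. Daily collection is stated for corticosteroids only, so time-varying covariates may be limited.
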